### 14.2 The number of subjects planned to be enrolled.

#### 14.2.1 Antibody measures:

Lack of any measurable antibody to both PT and PRN is the best available indicator of susceptibility to severe pertussis. Accordingly, we have based sample size calculations on reduction in the proportion of susceptible infants as early as possible. If superiority of birth pertussis vaccine is defined as a reduction of 12% or more in the proportion of subjects

lacking antibody (no measurable PRN or PT) compared with controls at 10 weeks old, a sample size of 220 in each maternal arm will have 80% power to detect a reduction of this magnitude at a two-sided alpha level of 0.05. This is not altered by a differing prevalence of detectable pre-immunisation antibody among controls over the range of 65% to 75%. (Sample Power V2 [www.spss.com](http://www.spss.com)) This study will recruit 110 participants in each of the 4 arms, a total of 440 participants allowing for a 10% drop out rate.

#### *14.2.2 Cell mediated immunity:*

Based on our pilot data, a sample size of 22 participants in each of the 4 arms will allow us to detect a difference of greater than 0.25 in log IL-5 with a power of 90% at the alpha level of 0.01. An actual sample size of 25 per group will allow for subject dropouts.

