#### *2.4.4 Cellular immune responses:*

Our pilot study showed that infants who received Pa vaccine at birth had a significant increase in IL5 and IL13 cytokine (TH2) responses to pertussis vaccine antigens at 7 months compared to those vaccinated later. There were no differences in IFN $\gamma$  and cytokine (TH1) responses to other vaccine antigens between groups. This suggests that birth Pa vaccine results in a TH2 bias, restricted to pertussis responses, compared to controls and raises the question of altered responses following subsequent natural pertussis exposure. Detailed profiling of infant T-cell immunity in response to neonatal pertussis vaccination is thus an essential component of this study.

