## 3.2 HYPOTHESES

1. IgG antibody responses to pertussis toxin (PT) and pertactin (PRN) in infants receiving monovalent acellular pertussis vaccine (Pa) at birth and routine vaccines at 6 weeks are significantly higher than in unvaccinated infants by 10 weeks of age, and remain higher at 6 and 8 months of age
2. Cell-mediated immune responses to PT and PRN at 10 weeks and 8 months of age in infants receiving monovalent acellular pertussis vaccine at birth and routine vaccines at 6 weeks do not differ significantly from those in infants with first doses at 6 weeks.
3. IgG antibody responses to **PT and PRN** at each time point in infants of mothers vaccinated with dTpa within the previous 5 years do not differ significantly from infants of unvaccinated mothers.
4. In infants receiving Pa at birth and routine vaccines at 6 weeks, the prevalence of antibody levels consistent with protection to **other vaccine antigens** is not significantly reduced
5. The frequency, duration and intensity of solicited symptoms in the 6 days following vaccination and unsolicited symptoms until the next vaccination visit (up to 8 months old) will not differ significantly between the infants receiving Pa vaccine at birth and controls.

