## 4 Study Objectives and Endpoints

### 4.1 Primary

To establish if earlier protection from severe disease due to *Bordetella pertussis*, as measured by PT and PRN antibody (Ab) and cell mediated immune (CMI) responses, is achieved by monovalent acellular pertussis vaccine (Pa) at birth *versus* vaccination schedules commencing at 6 weeks of age.

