### 4.2 Secondary

1. To determine whether maternal receipt of adult-formulated acellular pertussis vaccine (dTpa) within the previous 5 years influences infant Ab or CMI responses.
2. To evaluate interactions with vaccine antigens given concurrently at birth (hepatitis B) or later
3. To evaluate adverse clinical or immunological effects from early use of Pa vaccine.

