### **14.3 The level of significance to be used.**

Hypothesis tests and confidence intervals will be two-sided with alpha set to 5%.

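### Cell-mediated immunity is listed as a measure of protection in the primary objective but is expected not to differ in hypothesis 2, where mere non-significance, without a margin, would count as confirmation

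*Protocol*

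**What the plan says.** - **Primary objective (Protocol 4.1).** Earlier protection from severe disease is to be established "as measured by PT and PRN antibody (Ab) and cell mediated immune (CMI) responses". CMI stands beside antibody, and no direction or criterion is given for it.
- **Hypothesis 2 (Protocol 3.2).** CMI responses to PT and PRN at 10 weeks and 8 months in the birth group "do not differ significantly from those in infants with first doses at 6 weeks".
- **Pilot result (Protocol 2.4.4).** Infants given the vaccine at birth "had a significant increase in IL5 and IL13 cytokine (TH2) responses to pertussis vaccine antigens at 7 months". The protocol's reading is: "This suggests that birth Pa vaccine results in a TH2 bias". It adds that this raises a question about responses to later natural exposure.
- **Secondary objective 3 (Protocol 4.2).** "To evaluate adverse clinical or immunological effects from early use of Pa vaccine".
- **CMI sample size (Protocol 14.2.2).** 22 infants in each of four arms, to "detect a difference of greater than 0.25 in log IL-5 with a power of 90% at the alpha level of 0.01", raised to 25 for dropouts. No SD, log base or sidedness is given.
- **Significance level (Protocol 14.3).** "Hypothesis tests and confidence intervals will be two-sided with alpha set to 5" per cent, with no exception for CMI.
- **Primary analysis (Protocol 14.1).** The week-10 rate of infants without measurable antibody, by chi-square test. CMI is not part of it.

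**The concern.** CMI has no single role. As a measure of protection in 4.1, a favourable answer would be a difference between the groups. Under hypothesis 2 the expected answer is no difference. Under 2.4.4 and secondary objective 3, a difference in the TH2 cytokines is a possible harm.

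The practical consequence lies in hypothesis 2. As worded, it is confirmed by any non-significant test. The subset was sized to detect 0.25 log, so a smaller real shift has a fair chance of being non-significant, and nothing in the protocol prevents that from being reported as absence of a shift. The pilot pointed to this very effect, and 2.4.4 calls T-cell profiling an essential part of the study. The trial is also open-label, so the reading should be fixed before results are seen.

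**Working it through.** **1. Roles side by side**

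| Place | Role of CMI | Result looked for |
|---|---|---|
| 4.1 | Measure of earlier protection | Difference in favour of the birth dose (implied) |
| 3.2, hypothesis 2 | Comparability | No significant difference |
| 2.4.4; 4.2, objective 3 | Possible immunological harm | Whether there is a TH2 shift |
| 14.1, primary analysis | None | Not applicable |
| 14.2.2 | Basis for subset size | Detection of 0.25 in log IL-5 |

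This conflict needs no arithmetic.

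**2. The plan's own figure**

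Inputs from 14.2.2: n = 22 per arm, difference 0.25, power 90%, alpha 0.01 (taken as two-sided). The SD is not stated, so 22 cannot be reproduced independently. It can only be solved for the SD.

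Normal approximation: SD = 0.25 / (2.576 + 1.282) × √(n/2).
- Sizing for 22 v 22 (within a maternal stratum): 0.25 / 3.857 × √11 = 0.215. By noncentral t it is 0.206.
- Sizing for 44 v 44 (strata pooled): 0.25 / 3.857 × √22 = 0.304. By noncentral t it is 0.298.

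Both SDs are assumptions. The t-based values are carried forward.

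**3. What the 0.01 does**

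At SD 0.206 and 22 v 22, power for 0.25 is 90% at 0.01 and 97.5% at the 5% of 14.3. By the normal approximation, 90% power at 5% would need about 16 per arm. Sizing at 0.01 therefore adds infants and power.

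**4. Chance that a real shift is non-significant at 5%**

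SE = SD × √(2/n). For 22 v 22 at SD 0.206: 0.206 × √(2/22) = 0.0622. The smallest significant difference is 2.018 × 0.0622 = 0.126 log.

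| True shift (log) | Power at 5%, 22 v 22 | Missed |
|---|---|---|
| 0.10 | 0.349 | 65% |
| 0.15 | 0.654 | 35% |
| 0.20 | 0.881 | 12% |
| 0.25 | 0.975 | 2.5% |

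Pooling matters. At the same SD with 44 v 44, power for 0.15 is 0.921, so about 8% are missed. If the sizing was already for the pooled comparison (SD 0.298), the same noncentral t calculation for 44 v 44 again misses about 35% at 0.15.

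**5. Would a confidence-interval rule work with the planned samples?**

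Pooled 95% half-width = t × SD × √(2/n).

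| SD assumed | 44 per group | 50 per group |
|---|---|---|
| 0.206 | 1.988 × 0.0440 = 0.087 | 1.984 × 0.0413 = 0.082 |
| 0.298 | 1.988 × 0.0636 = 0.126 | 1.984 × 0.0596 = 0.118 |

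For an interval inside ±0.25, the observed difference must be below 0.25 minus the half-width: 0.163 to 0.168 at the smaller SD, 0.124 to 0.132 at the larger. In the worst case (0.124 with SE 0.0636) that limit is 0.124 / 0.0636 = 1.95 standard errors from zero. With no true shift the rule would then succeed about 95% of the time.

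**The case against.** The strongest reply is that little turns on this. The formal primary analysis is antibody only, so CMI can neither rescue nor overturn it. Section 2.4.5 ties presumed protection to measurable IgG to PT and PRN. Section 4.1 asks an open question and sets no CMI criterion. A margin and decision rule are often left to the SAP, which is not at hand. All of this stands, and it limits the point to the role of CMI and the reading of hypothesis 2. It does not remove it: 4.1 and hypothesis 2 conflict within the protocol itself, and hypothesis 2 already fixes non-significance as its standard.

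Two stronger readings are tempting, and the protocol does not support them.

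- A reader might infer that the 0.01 of 14.2.2 and the 5% of 14.3 are rival test levels, so that a TH2 shift with p between 0.01 and 0.05 could be dismissed by choosing the stricter one. But 14.2.2 falls under the number of subjects planned, and 14.3 governs all tests and intervals. Such a result is significant under the protocol.
- A reader might infer that an IL-5 rise could be reported as evidence of protection. Section 4.1 does not name IL-5, and where the protocol interprets a rise, in 2.4.4, it treats it as a concern.

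A fair technical objection is that the magnitude rests on an SD the protocol does not give. That is why two SDs are shown.

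**Conclusion.** The point holds in a limited form. CMI is given conflicting roles in 4.1 and 3.2, and hypothesis 2 treats absence of significance as evidence of no difference, with no margin, in a subset sized to detect a difference. A TH2 shift smaller than 0.25 log could therefore be reported as no difference. At SD 0.206 a true 0.15 log IL-5 shift is missed about 35% of the time within a stratum and about 8% with 44 per group pooled. If the sizing was for the pooled comparison (SD 0.298), the pooled figure is again about 35%. These figures assume a two-sided 0.01 in 14.2.2, roughly normal log IL-5 with equal variances, and the back-solved SD. The conflict between the sections depends on none of them. The primary antibody comparison and its 5% level are untouched, and the 0.01 is not an error.

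**What to change.** 1. Remove CMI from 4.1 and make it a secondary objective with one stated role: assessing whether the birth dose produces a pertussis-specific TH2 shift. Name IL-5 and IL-13 with IFN-gamma alongside, since a TH2 shift is relative to TH1, and name both time points, 10 weeks and 8 months.
2. Reword hypothesis 2 as an estimate: the birth-minus-control difference in log cytokine response, maternal strata pooled and adjusted for, with a 95% confidence interval. Conclude that there is no relevant shift only if the interval lies within a margin fixed and justified before results are seen. The 0.25 log planning difference is a candidate upper limit for IL-5, but it was chosen as a difference to detect, so the sponsor must justify it or set a smaller one. IL-13 and IFN-gamma need their own margins.
3. In 14.2.2, state the SD, the log base and whether the sizing is within stratum or pooled. Add that 0.01 is for planning only and that tests follow 14.3.

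The cost is wording in the objectives, hypotheses and statistics sections. No extra samples are needed for a 0.25 margin; a tighter one would need its own check. The downside for the sponsor is that no difference has to be shown, so an inconclusive result becomes possible.

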### **14.3 The level of significance to be used.**

Hypothesis tests and confidence intervals will be two-sided with alpha set to 5%.

### **14.4 Statistical criteria for the termination of the trial.**

There are no formal statistical stopping rules for this study.

### **14.5 Procedure for accounting for missing, unused and spurious data.**

From an analysis perspective, a 'drop-out' will be any subject who did not attend the concluding visit. A participant, who returns for the concluding visit in the protocol, even if not all prior visits were attended, is deemed to have completed the study.

Methods for imputing missing values (e.g. last post-baseline observation carried forward) or analysis models that accommodate missing data (e.g. repeated measures mixed-models) will be employed where necessary to ensure as many subjects as possible from the Full Analysis Set contribute to the efficacy analyses.

### **14.6 The selection of subjects to be included in the analyses**

The Full Analysis Set will comprise all randomized participants. The Safety Analysis Set will comprise all randomized participants that receive at least one vaccination

## **15 Direct Access to Source Data/Documents**

The sponsor should ensure that it is specified in the protocol or other written agreement that the investigator(s)/institution(s) will permit trial-related monitoring, audits, IRB/IEC review, and regulatory inspection(s), providing direct access to source data/documents.

The investigators undertake to maintain complete written documentation of trial procedures, which are open to inspection for monitoring and audit by nominated representatives of the sponsor. These records are further open to review by independent ethics committees and regulatory authorities such as the Therapeutic Goods Administration.

## **16 Quality Control and Quality Assurance**

Recruitment in an acceptable time frame requires multi-centre collaboration for a study of this type. All investigators have extensive experience in the conduct of infant vaccine trials, including recruitment at birth and are confident of targets of 110 subjects per centre. The trial

groups in Sydney, Melbourne, Adelaide and Perth have extensively collaborated in research level over the last ten years.

## **17 Ethics**

This study will be conducted according to Good Clinical Practice as defined by the International Conference on Harmonisation. The study protocol will vary from standard immunisation practices only in the earlier provision of Pa vaccine to newborn infants in group 1 and the administration of the first dose of Pa containing vaccine at 6 weeks old in infants in both groups, replacement of Prevenar with Synflorix and the collection of blood samples. The infants will each receive immunisation for all age-appropriate antigens specified in the Australian Immunisation Handbook (currently 9th edition ) except that the first standard vaccine will be given from 6 weeks of age, two weeks earlier than the current schedule age of 8 weeks (2 months). The Pa combination vaccine, used at this age, is licensed for use from 6 weeks old and is considered a valid dose by ACIR. The infants will be under the care of medical and nursing staff expert in the administration of vaccinations to infants and the collection of blood samples from infants. There are few data on responses to DTPa vaccines in infants younger than 6 weeks. There are no grounds to suggest earlier administration will be harmful (see background for further discussion).

## **18 Data Handling and Record Keeping**

Each study centre will maintain an individual file and source documentation for every participant enrolled in the study. The file will include visit dates of the participant, along with relevant demographic information. The file will further document participant eligibility for the study as well as any serious adverse reactions experienced and other notes as appropriate. An electronic CRF must be completed for each enrolled participant and will be checked against the source documents to ensure data completeness and accuracy as required by the study protocol.

The eCRF and source documents will be kept in order and up to date so that they always reflect the latest observations on the participants enrolled in the study. The source documents will be securely stored in locked cabinets and will only be accessed by appropriately trained staff at each study centre and the electronic eCRF will comply with applicable privacy laws.

The original, signed consent form will be filed with each participant's source documentation.

All eCRFs must be signed off by the local Investigator (or their delegate) on completion of the study.

All study forms for each enrolled infant will be stored securely. Data will be entered into a database, designed to have appropriate data checks. Access to databases will be restricted by password. Back up copies of the forms and database will be made and stored separately. Data will not be collected from any federal government agency e.g. Medicare. Data will be stored securely for a period up to 30 years or as required by standard trial procedures.

## **19 Financing and Insurance**

GSK Biologicals has agreed to supply the monovalent acellular pertussis and Synflorix vaccines and perform antibody measurement and has a clinical trial agreement with each of the four study centres.

This trial is supported by an NHMRC project grant (No 570756)

Each site will indemnify its own staff engaged in study conduct according to existing local arrangements.

